#### Secondary outcomes

Multilevel mixed model analysis will be used to assess differences in quality of life, anxiety states, and depressive symptoms between the conditions. We will start with a three-level structure, with respectively quality of life, anxiety states, and depressive symptoms as dependent variable, repeated measures at the first, individuals at the second, and treatment condition at the third level. Age, gender, Ehealth literacy scale scores, and medication use will be added as covariates.

#### Mediation analysis

In order to assess differences between the groups in self-efficacy and experiential avoidance, we will apply multilevel analysis with the scores on the SEQ-OCD and AAQ-II scores at baseline, midtest, and posttest will serve as dependent variables, treatment condition (ERP as usual versus personalized ERP) as a fixed (dichotomous) factor. Furthermore, we will use the macro of Preacher and Hayes and apply bootstrapping methods to assess the possible mediating effect of changes in self-efficacy and experiential avoidance on subsequent treatment effects.

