##### The Self-Efficacy Questionnaire for OCD (SEQ-OCD)

In order to measure patient’s self-efficacy regarding their OCD symptoms, we adapted the self-efficacy questionnaire for phobic situations (SEQ-PS). The SEQ-PS is a 13-item psychometric scale that is designed to measure the perceived ability to cope with phobic symptoms when approaching feared stimuli [36]. Responses are recorded on a 5-point scale. The SEQ-SP was found to have Cronbach’s alpha of 0.94. We adapted the SEQ-PS to measure symptoms of OCD when being confronted with the object of intrusions and not being able to perform compulsions. The SEQ-OCD will be included in all measurement moments.

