##### The Acceptance and Action Questionnaire II (AAQ-II)

The AAQ-II [37] is a 7-item measure of psychological inflexibility/experiential avoidance. Answers are given on a 7-point scale ranging from 1 = never true to 7 = always true. The Dutch translation of the AAQ-II has been found to have good psychometric properties [38]. Experiential avoidance has been found to play some role in the development of obsessive–compulsive symptoms but it remains yet unclear to what extent [15, 18, 19]. We included the AAQ-II to assess the possible role on symptom severity and treatment effect. The AAQ-II will be included in all measurement moments.

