## Data collection and management

### Plans for assessment and collection of outcomes {18a}

In our study, we will administer a combination of structured clinical interviews and self-report questionnaires. Clinical interviews will be administered by trained outcome assessors. Outcomes of the questionnaires will be collected through the software package Research Manager and stored in encrypted form on a secured server. Measurement moments will be at baseline, 5 weeks of treatment, 10 weeks of treatment (midtest), 15 weeks of treatment, 20 weeks of treatment (posttest), 6 weeks follow-up, 3 months follow-up, 6 months follow-up, and 12 months follow-up. Primary and mediation outcomes will be measured at all measurement moments. Secondary outcomes will be measured at baseline, midtest, posttest, and in all follow-up moments. Control variables will be measured at baseline. For more information on outcomes, see {12}.

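### The mediator group comparison leaves out T1 and T3, and the stated mediation test does not secure the time order it intends

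*Protocol article*

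**What the plan says.** Visit labels here follow the Abstract (T0 to T8, with posttest at T4), because Trial design {8} uses T3 and T4 twice.

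- **Objectives {7}:** two of the three objectives are mediation questions, one on experiential avoidance and one on self-efficacy. The Abstract calls mediation a secondary goal.
- **Data collection {18a}:** "Primary and mediation outcomes will be measured at all measurement moments". The instrument descriptions agree: "The SEQ-OCD will be included in all measurement moments" and "The AAQ-II will be included in all measurement moments". The Y-BOCS is also given at every assessment.
- **Outcomes {12}:** the primary outcome is the fall in Y-BOCS from baseline to posttest.
- **Mediation analysis, first step:** a multilevel comparison of the arms in which "scores on the SEQ-OCD and AAQ-II scores at baseline, midtest, and posttest will serve as dependent variables".
- **Mediation analysis, second step:** the plan is to run the Preacher and Hayes macro and "apply bootstrapping methods to assess the possible mediating effect of changes in self-efficacy and experiential avoidance on subsequent treatment effects". This sentence names no visits and no adjustment for earlier Y-BOCS.
- **Additional analyses {20b}:** none are planned.

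**The concern.** A mediation claim needs the mediator to move before the outcome, and needs some protection against the reverse path, in which patients who improve come to feel more able to cope or less avoidant. The visit schedule supplies the data for this: five aligned measurements of mediator and outcome during treatment. The stated analysis makes little use of them. The group comparison omits two of the five visits without a reason. The mediation test is built on mediator changes and leaves open when those changes end and when the later effect begins.

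One permissible reading takes mediator change over T0–T4, the span of the primary outcome. Nothing in that window is then later than the mediator, and improvement that feeds back on the mediator can look like an indirect effect. The interpretation of objectives 2 and 3 is at stake. The comparison of the arms on Y-BOCS is not.

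**Working it through.** **Visits.** The mediators are collected at 9 visits (T0–T8), 5 of them from baseline to posttest. The stated group comparison uses 3. It therefore omits 5 − 3 = 2 in-treatment visits, T1 (week 5) and T3 (week 15).

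**Plan's own figure.** There is none to reproduce, because the article gives no effect size, power or sample size for mediation. The total of 160 belongs to the main comparison and is used below only as the number of patients.

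**Simulation.** All parameters except N = 160 and 1:1 allocation are assumed. With X for arm, Y for Y-BOCS and M for the mediator, in standardised units:

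- Baseline: Y and M with SD 1 and correlation 0.3.
- Each later visit: Y(t) = 0.7·Y(t−1) + p·X + q·M(t−1) + error, and M(t) = 0.7·M(t−1) + r·X + s·Y + error, with error SD 0.6. Y in the second equation is taken at visit t or t−1, depending on the scenario.
- Indirect effect: a·b, where a is the coefficient of X in the mediator regression and b is the coefficient of M in the outcome regression that also contains X. Mediation is declared when the 95% percentile bootstrap interval (300 draws) excludes zero. There were 400 trials per scenario.

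Three readings of the plan were compared:

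- **A:** mediator change T0–T4 and outcome change T0–T4.
- **B:** mediator change T0–T2 and outcome change T2–T4.
- **C:** mediator at T2 and outcome at T4, with baseline mediator and baseline Y in both regressions and Y at T2 in the outcome regression.

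| Scenario | A | B | C |
|---|---|---|---|
| No mediation; Y drives M at the same visit (p = −0.2, s = 0.3) | 28.8% | 9.8% | 1.0% |
| No mediation; Y drives M one visit later (p = −0.2, s = 0.3) | 1.8% | 5.0% | 0.2% |
| No effects of any kind | 1.2% | 0.8% | 0.0% |
| True lagged mediation (r = −0.2, q = 0.2) | 14.8% | 45.8% | 74.2% |

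The first three rows are false declarations and the last is correct detection. The simulation standard error is √(p(1−p)/400), with p here the tabled rate: for 28.8%, √(0.288 × 0.712/400) = 2.3 points; for 1.0%, √(0.010 × 0.990/400) = 0.5 points.

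**Second check, same-window reading only.** Here mediator change was generated purely as a consequence of Y-BOCS change (1000 trials per setting, 500 bootstrap draws). False mediation was 10.1%, 21.5% and 33.6% for d = 0.35 with mediator–outcome correlation 0.3, 0.5 and 0.7. For d = 0.5 it was 17.2%, 34.1% and 61.2%.

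The answer therefore turns on the windows and the adjustment, which the article leaves open. Model C uses only T0, T2 and T4, so its gain comes from time order and adjustment for earlier Y-BOCS. A lagged model over all five visits was not simulated.

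**The case against.** The strongest reply is that the mediation sentence is not wrong as written and that its details may sit in an analysis plan not shown. Much of this stands, and it rules out several stronger readings that a reader might infer:

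- **That the mediation test itself uses only three visits.** The three-visit limit is written for the multilevel group comparison. The bootstrap sentence names no visits.
- **That the plan cannot separate mediation from its reverse.** The word *subsequent* signals an intended order. An early-mediator, later-outcome analysis fits the sentence, and adjustment for earlier Y-BOCS is neither stated nor excluded.
- **That any outcome after posttest is confounded by outside care.** Concomitant care {11d} describes a treatment-free period of 6 weeks, and free help-seeking starts only after the booster session that follows. The 6-week follow-up (T5) falls at the end of that break. It lies outside the primary T0–T4 window, however.
- **That the macro ignores nesting or discards incomplete patients.** The article does not say whether the model is single-level or how missing values are handled. With one row per patient, no repeated measures would remain to be nested.
- **That rates of 34% to 61% are this plan's error rate.** They belong to an assumed same-window, purely reverse-causal set-up. With a one-visit lag, the same-window reading gave 1.8%.
- **That objectives 2 and 3 would go unanswered.** That follows only on the worst reading.

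Omitting T1 and T3 also does not bias a randomised comparison of mediator levels; it loses information. What the reply does not remove is that the three-visit choice is stated, not left open. Even the favourable reading B, without adjustment for earlier Y-BOCS, gave 9.8% false mediation in one scenario and detected true mediation less often than C.

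**Conclusion.** The point holds in a limited form. The article leaves two of the five in-treatment visits out of the mediator group comparison. It also states a mediation test whose intended time order nothing in the text secures. Across the two assumed reverse-causation scenarios, false mediation ranged from 1.8% to 28.8% for same-window change scores and from 5.0% to 9.8% for early-mediator, later-outcome change scores. It was 1.0% or less for a lagged model adjusted for prior Y-BOCS. In one assumed scenario of true lagged mediation, detection was 14.8%, 45.8% and 74.2% respectively.

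These figures rest on assumed effects, autocorrelation and lags. They show how far the result depends on choices left open and do not estimate the error rate of this trial. The change is worth making because mediation makes up two of the three objectives.

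**What to change.** 1. Use T0, T1, T2, T3 and T4 in the multilevel group comparison of SEQ-OCD and AAQ-II.
2. Base the mediation test on a lagged model within T0–T4, in which the mediator at one visit predicts Y-BOCS at a later visit. Adjust for prior Y-BOCS and prior mediator, put treatment on both paths, fit to all available data, and give a bootstrap or Monte Carlo interval for the indirect effect.
3. At minimum, take mediator change T0–T2 and Y-BOCS at T4, adjusted for Y-BOCS at T0 and T2. Adding the baseline mediator brings this close to model C above.

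The cost is more analysis work and added modelling assumptions: the chosen lag must suit the process, and unmeasured common causes of mediator and outcome remain possible. Adjusting for T2 Y-BOCS also confines the minimum version to the part of the effect that arises between T2 and T4. No new data are needed and the primary comparison is unaffected.

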### Interim analyses {21b}

Non applicable, no interim analyses will be done.

### Methods for additional analyses (e.g., subgroup analyses) {20b}

Non applicable, no additional analyses are planned.

### Methods in analysis to handle protocol non-adherence and any statistical methods to handle missing data {20c}

All data will be analyzed according both to the intention-to-treat and per protocol principle in order to gain as much insight as possible into the efficacy of the intervention, as recommended by CONSORT.

### Plans to give access to the full protocol, participant-level data, and statistical code {31c}

We will provide access to participant-level data without any kind of demographic information, to ensure anonymity of the participants. Data and statistical code will be provided by the corresponding author at request.

## Oversight and monitoring

### Composition of the coordinating center and trial steering committee {5d}

This trial is being conducted within PsyQ, center The Hague. PsyQ is part of the Parnassia Groep, a large urban ambulatory mental health organization in the Netherlands. The study will be monitored once a year according to the Standard Operating Procedure monitoring within the Parnassia Groep. PsyQ has appointed a Research Committee (CWO) to oversee all scientific studies in the organization. The CWO consists of multiple researchers, at least one professor, a methodologist, and a manager responsible for the quality of care. The committee gathers every 3 months. All studies conducted within PsyQ are monitored once a year to ensure the quality of medical-ethical concerns, the storage of data, and progression of recruitment. In addition, the Parnassia Groep has appointed a Central Research Committee (CCOI) who is responsible for quality assessment of all studies within the Parnassia Groep. Once a year, this committee will consult the local CWO in regard to quality assessment and progress regarding the ongoing studies.

### Composition of the data monitoring committee, its role and reporting structure {21a}

Not applicable. Since our treatment is not expected to be harmful and all our participants are likely able to express themselves, no data safety monitoring board is established.

### Adverse event reporting and harms {22}

No serious adverse events are to be expected, but when a serious adverse event occurs the same procedures will be followed as in routine treatment. Depending on the seriousness of the adverse events, measures will be taken. In the current project, 1 psychiatrist per department is connected to the study who can be consulted in case of emergencies.

The investigator will report all SAEs to the sponsor without undue delay after obtaining knowledge of the events. The sponsor will report the SAEs through the web portal *ToetsingOnline* to the accredited METC that approved the protocol, within 7 days of first knowledge for SAEs that result in death or are life threatening followed by a period of maximum of 8 days to complete the initial preliminary report. All other SAEs will be reported within a period of maximum 15 days after the sponsor has first knowledge of the serious adverse events.

### Frequency and plans for auditing trial conduct {23}

The sponsor/investigator will submit a summary of the progress of the trial to the accredited METC once a year. Information will be provided on the date of inclusion of the first subject, numbers of subjects included, and numbers of subjects that have completed the trial, serious adverse events/serious adverse reactions, other problems, and amendments.

### Plans for communicating important protocol amendments to relevant parties (e.g., trial participants, ethical committees) {25}

Amendments are changes made to the research after a favorable opinion by the accredited METC has been given. All amendments will be notified to the METC and updated in the trial register.

### Dissemination plans {31a}

The results of this trial will be published in peer-reviewed journals and presented on relevant conventions. Also, a summary of the results will be sent to all participants.

## Discussion

This paper described the study protocol of an RCT comparing traditional exposure to personalized exposure. Personalized exposure will be offered through video-calling in the environment of the participant, with the intention to increase the ecological validity of the ERP. ESM data will be collected and used as an intervention to personalize the exposure further. We will compare personalized exposure with exposure as usual, provided in the treatment room of the therapist.

## Limitations

There are some limitations to consider.Since our study is combining two interventions in the experimental condition, both the use of video-calling and an ESM intervention, a possible effect cannot be attributed to either one of the interventions. We believe that the severity and persistence of OCD justifies our choice for this so-called “black-box design”.Participants are not blinded for treatment allocation when filling out baseline measures, making them susceptible for attrition bias. However, to date, there has been almost no attrition pre-treatment (*N* = 1), and this attrition could not be attributed to treatment allocation.There is no waitlist condition in our design. Although there are many arguments against using a non-active condition, the lack of it may influence the internal validity of this study. If we find a possible effect, it cannot be determined to what extent the factor time has influenced the symptoms of participants. We do however believe that the risk of this is minimal since OCD is such a persistent disease with relatively stable symptom strength over time.Although one of our inclusion criteria is that possible medication use needs to be stable for 12 weeks, we did not gather information regarding the dosage being used. Since patients with OCD need higher doses of medication compared to other anxiety disorders, this lack of information may compromise the internal validity of this study [50]. We do however believe that this risk is minimal since we control for medication use (yes/no) in our statistical model.

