### Outcomes {12}

#### Primary outcome measure

##### Yale-Brown Obsessive–Compulsive Scale (Y-BOCS)

Primary outcome is a decrease in symptom severity, measured with the Y-BOCS, between the measurements taken at baseline and at posttest.

The Y-BOCS is a semi-structured clinical interview which assesses the severity of obsessions and compulsions separately and is the gold standard to measure OCD severity in clinical practice and scientific research. The Y-BOCS consists of 10 items which are rated on a 4-point Likert scale. The internal consistency and validity of the Y-BOCS have proven to be good. Moreover, the Y-BOCS is sensitive to change. The Y – BOCS has been validated in a Dutch clinical population [30]. The Y-BOCS will be administered at each assessment moment by telephone by trained outcome assessors.

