## Assignment of interventions: blinding

### Who will be blinded {17a}

Since we are investigating two active treatment conditions, both participants and therapist will not be blinded to assignment. All outcome assessors and data analysts will be blinded for intervention assignment.

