## Statistical methods

### Statistical methods for primary and secondary outcomes {20a}

#### Primary outcomes

Multilevel mixed modelling analysis will be used to investigate differences in treatment effect, measured through symptom reduction on the Y-BOCS. Multilevel analysis is especially suitable to analyze repeated measurement data because it takes into account the dependencies among observations nested within individuals. Another advantage of this methodology is its ability to handle missing data. We will start with a three-level structure with treatment effect (Y-BOCS score) as dependent variable, repeated measures at the first, individuals at the second, and treatment condition at the third level. We will then add age, gender, Ehealth literacy scale scores, and medication use to the model as covariates. We will determine the covariance structure empirically. Effect sizes and clinical significant change according to the Jacobson and Truax criteria will be calculated to estimate respectively the magnitude of the treatment effect and the significance of the results for clinical practice [49]. All analyses will be done both according to the intention-to-treat principle and per protocol in order to gain as much insight as possible into the efficacy of the intervention, as recommended by CONSORT.

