## Trial status

This trial is registered in the Netherlands trial register on December 19, 2019. Initial recruitment started in January 2020; however, it had to be halted due to COVID–19 measures in the Netherlands. Due the fact that all participants in the face-to-face control condition received treatment via video-calling, almost all data collected between January 2020 and May 2020 was not usable; therefore, inclusion was restarted with a new sample in June 2020. To date, 102 participants have been included, we anticipate to reach the full sample size around July 2024.

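### Participants know their arm when they complete the baseline measures, and the stated limitation covers drop-out but not arm-dependent baseline answers

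*Protocol article*

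**What the plan says.** The order of disclosure and baseline is given in the Limitations section of the protocol article: "Participants are not blinded for treatment allocation when filling out baseline measures, making them susceptible for attrition bias". The answer offered there is that "there has been almost no attrition pre-treatment", with N = 1, and that this one loss was not due to allocation. No section discusses whether knowing the arm could change the baseline answers themselves.

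Baseline is used in three ways.

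- **Primary outcome.** "Primary outcome is a decrease in symptom severity, measured with the Y-BOCS, between the measurements taken at baseline and at posttest".
- **Mediators.** The SEQ-OCD and AAQ-II are taken at every assessment, and the mediation section analyses them from baseline through midtest to posttest.
- **Covariate.** Under Plans for assessment {18a}, "Control variables will be measured at baseline"; the eHLQ is listed among these variables. The primary analysis then states: "We will then add age, gender, Ehealth literacy scale scores, and medication use to the model as covariates". The secondary models use the same covariates.

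On blinding, section {17a} leaves participants and therapists unblinded but says: "All outcome assessors and data analysts will be blinded for intervention assignment". For the Y-BOCS: "The Y-BOCS will be administered at each assessment moment by telephone by trained outcome assessors".

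**The concern.** A baseline value serves as a reference because allocation cannot have influenced it. Once participants know their arm, that guarantee is gone. Hope or disappointment about treatment through an app, or in the clinic, can move answers on self-efficacy, experiential avoidance, quality of life, depression and anxiety, and can do so differently by arm. Some eHLQ scales, such as motivation to use digital services and feeling safe and in control, concern the very thing that separates the arms.

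The limitation names one consequence, attrition, and shows it to be small. A reader is reassured about that risk and not told of the other. If T0 answers do shift by arm, the shift enters every contrast measured from T0. Adjusting for an eHLQ score that allocation has moved can add to or take away from the estimated treatment effect.

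**Working it through.** **Reading the sections together.** The Limitations statement is explicit that allocation is known when baseline measures are filled out. The Concealment section, where one research assistant knows the allocation and the other measures blinded, is consistent with this but does not itself date T0. The timeline figures are not shown. The self-report scales and the eHLQ therefore fall under the statement directly. For the Y-BOCS, a telephone interview, the order is likely but not spelled out.

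**Size of a possible bias (illustration only).** The plan gives no figure to reproduce.

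Inputs:
- 160 patients, taken as 80 per arm (Sample size; 1:1 ratio under Sequence generation)
- correlation between measurements rho = 0.5 and alpha 0.05 (Sample size)
- two-sided testing: my assumption, as the article does not state it
- a shift of s SD in one arm at T0 and none at posttest (T4): my assumption

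Formulas, in SD units:
- Change score: bias = s; SE = sqrt(2(1 - rho)) x sqrt(2/80) = 1 x 0.158 = 0.158
- Baseline-adjusted: bias = rho x s; SE = sqrt(1 - rho^2) x sqrt(2/80) = 0.866 x 0.158 = 0.137
- Type I error = 1 - Phi(1.96 - bias/SE) + Phi(-1.96 - bias/SE)

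| s (SD) | Change-score bias | Type I error | Adjusted bias | Type I error |
|---|---|---|---|---|
| 0.05 | 0.05 | 6.2% | 0.025 | 5.4% |
| 0.10 | 0.10 | 9.7% | 0.05 | 6.5% |
| 0.20 | 0.20 | 24.4% | 0.10 | 11.3% |

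For s = 0.10: 0.10/0.158 = 0.63 gives 9.7%, and 0.05/0.137 = 0.37 gives 6.5%.

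Adjusting for baseline halves the bias at rho = 0.5 but does not remove it. At a higher correlation it removes less: at rho = 0.7 a shift of 0.1 SD leaves 0.7 x 0.1 = 0.07 SD. The listed covariates do not include the baseline Y-BOCS, and the article does not fix how T0 enters the repeated-measures model, so both columns are relevant.

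**Relative to the planned effect.** The Sample size section labels its effect f = 0.35. Taken literally for two groups, that is d = 0.70, and a 0.1 SD bias is 0.1/0.70 = 14% of it. If 0.35 is meant as a standardised mean difference, the share is 0.1/0.35 = 29%.

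**The eHLQ.** If disclosure moves the eHLQ by delta between arms and the within-arm slope of outcome on eHLQ is beta, adjustment changes the treatment estimate by beta x delta in size. The article gives neither quantity, so no number can be attached.

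**Patients still to come.** Under Trial status: "To date, 102 participants have been included, we anticipate to reach the full sample size around July 2024". That leaves 160 - 102 = 58 at the time of the article, and fewer with each later inclusion.

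**The case against.** Four points count on the other side.

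1. **The Y-BOCS is a blinded-assessor interview.** The statement about filling out measures may refer mainly to questionnaires. Assessor blinding removes rater bias but not the effect of an unblinded participant's own answers. The risk to the primary outcome is therefore possible rather than established, and clearest elsewhere.
2. **A shift at T0 alone is a worst case for change scores.** Participants stay unblinded throughout. If a fraction k of the shift persists to T4, the change-score bias falls to (1 - k) x s and vanishes at k = 1. This stands, and the table is conditional on k = 0.
3. **The eHLQ may not move much.** Some of its scales concern competence and understanding, and nothing in the article shows that allocation shifts them. The primary analysis also starts without the covariates, so an estimate without the eHLQ will exist. What remains is that the article does not say which model is confirmatory.
4. **Attrition bias is a genuine risk here.** People can leave on learning their arm, and the authors disclosed the underlying fact themselves. The label is incomplete rather than wrong.

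A reader might go further and infer that the primary result is already biased or that the true error rate is 9.7% or 24.4%. The documents do not support that: they give no evidence of any shift, its direction or its size.

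**Conclusion.** The point holds as a gap in design and in the stated limitation. Knowledge of allocation at baseline is the article's own statement, and the low pre-treatment drop-out does not answer the risk of arm-dependent answers. Exposure is clearest for the SEQ-OCD, AAQ-II, WHOQOL-Bref, QIDS, STAI and eHLQ, and possible for the Y-BOCS if its T0 interview follows disclosure. The primary change, the mediator analyses and the eHLQ-adjusted models can be biased.

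The size is unknown. The illustrative type I errors (6.5% to 9.7% for 0.1 SD; 11.3% to 24.4% for 0.2 SD) rest on a shift in one arm at T0 only, 80 per arm, rho = 0.5 and two-sided testing. They show that a modest shift would matter, not that one occurred. The change is worth making because it is cheap and part of it can still be made after recruitment ends.

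**What to change.** - **Patients not yet randomised** (at most 58 at the time of the article): complete and lock the whole T0 battery, including Y-BOCS and eHLQ, before the patient is randomised and the result disclosed.
- **Patients already enrolled:** record for each whether T0 came before or after disclosure. A comparison of the two groups is descriptive only, because it is confounded with calendar time.
- **Confirmatory model:** name the model without the eHLQ, keeping age, gender and baseline medication use. Show the eHLQ-adjusted model as a sensitivity analysis.
- **Sensitivity analysis:** compare posttest scores without T0 as reference. At rho = 0.5 its SE, sqrt(2/80) = 0.158 SD, equals that of the change score. It removes a T0 shift but not any effect of unblinded answers at posttest.
- **Limitations text:** add response or expectation bias at baseline alongside attrition bias, and say whether the T0 Y-BOCS interview also follows disclosure.

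The cost is a changed order of two existing steps for the remaining patients and a little more analysis work. The analysis and wording changes remain possible even if recruitment has closed.
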